**Figure 2 ztag055-F2:**
[figure not shown]
Flow diagram of patient inclusion/exclusion criteria.

### Outcomes

The primary endpoint of the study will be worsening of renal function. Early detection or prediction of WRF provides an opportunity for intervention to prevent progression to renal failure and acute kidney injury (AKI) and potentially prevent hospitalization and death. Serum creatinine was selected as the primary biomarker for modelling. While a retrospective glomerular filtration rate (eGFR) recalculation using a single formula (CKD-EPI 2021) was a way of standardizing the historical data, we decided on raw serum creatinine. This approach avoids any bias. The raw serum creatinine allows an ML model to learn the effect of age and gender on renal trajectories directly from raw data rather than being constrained by fixed eGFR coefficients. In addition, a 12-month prediction period has been chosen to align with routine chronic disease monitoring intervals in primary care, thereby bridging the gap between acute injury (AKI) and long-term disease progression. Therefore, WRF is defined by primary care data if any of the following occur within 12 months: (i) 30% increase in serum creatinine or (ii) 26.5 µmol/L increase in serum creatinine.

Secondary outcomes will include hospitalization for AKI, major adverse cardiovascular events (MACE) and all-cause mortality. These outcomes are included specifically to consider competing risks and to recognize that patients with HF may experience cardiovascular events or death before renal monitoring.

### Predictors

Data shall be presented in longitudinal panel data format. Although cohort eligibility is determined at the date of diagnosis of HF (index date), the longitudinal model trajectory is based on the first available serum creatinine (*t*_0_) measurement in each patient. If there is a gap between the index date and the first creatinine measurement, the static baseline covariates are shifted to *t*_0_. The longitudinal data will contain demographic information, lifestyle factors, co-morbidities and medication use associated with HF, renal decline, and mortality following a review of the literature on HF and renal function monitoring.^20–26^ The major factors for code list preparation are provided in *Table 1*. A full list of definitions for the planned predictor variables is provided (along with definitions of units of measurement, categories, and acceptable value ranges) in Supplementary File  *S2*. The code lists used to extract the relevant data and define the candidate predictors will be developed, curated, and validated by clinical experts within the RENAL-HF project team. All code lists will be made available in the GitHub repository: https://github.com/alxv/Renal-HF. The models will use two categories of predictors. Static predictors are baseline demographics (age, sex, ethnicity, deprivation index) and comorbidities observed at the index date. Dynamic predictors will be time-varying variables updated at each measurement point, including serum creatinine, other longitudinal laboratory tests (potassium, sodium, urea) and the status of active medicinal products. All models utilize data available up to the moment of prediction (*t*) to forecast outcomes at *t* + 1. Future data are never used for model development at time t.

**Table 1 ztag055-T1:** Major factors for code list preparation

Description	Factors
**Cardiovascular**	Blood pressure, hypertension, smoking status, atrial fibrillation, and ischaemic heart disease
**Renal**	Chronic kidney disease status, history of AKI, renovascular disease, dialysis, nephrectomy, proteinuria, nephritis, and anaemia
**Comorbidities**	Chronic liver disease, diabetes, systemic lupus erythematosus, and peripheral vascular disease
**Lab tests**	Haemoglobin, potassium, albumin, sodium, mean corpuscular volume, and urea
**Medication**	Non-steroidal anti-inflammatory drugs, drugs acting on the angiotensin system, specific antimicrobials, and immunosuppressants

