## Introduction

Approximately 15 million people in the Europe live with heart failure (HF), most of whom also have renal problems.^1^ In the UK as well as in other countries, most of these patients are managed in primary care. Modern therapy for people with HF comprises a combination of drugs, with dose titration being important to optimize control, and therefore improve prognosis. Sub-optimal treatment regimens and doses can lead to a progression of HF symptoms, and in turn worsen renal function. Conversely, over-treatment can also impair renal function. Either can lead to hospitalization and increases the risk of death.

There are no clear clinical guidelines on how renal function monitoring should be carried out in patients with HF. Even if population-based guidelines were available, they will be variably followed and may also be wasteful in terms of unnecessary testing for patients, increasing the burden on healthcare services and impairing the quality of life of patients. Hence, there is a need for tools that can inform primary care clinicians in the monitoring of renal function and guide treatment decisions.

The RENAL-HF project aims to develop an evidence-based system to support personalized renal function monitoring and treatment in patients with HF. Rooted in prediction technology, this system models the dynamic trajectory of renal function (serum creatinine) to predict the risk of worsening renal function (WRF) over a rolling 12-month horizon. Clinical prediction models (CPMs) are becoming increasingly important in modern clinical practice, informing healthcare professionals, patients, and families about the risks of outcomes, facilitating (shared) healthcare decision-making and improving health outcomes.^2^

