### Participants

The study population will consist of all patients with their first ever recorded diagnosis of HF between 1 January 2005 to 1 March 2022. We chose to use data after 2005 as the Quality and Outcomes Framework (QOF) was introduced in UK general practices in 2004 and resulted in improved recording in medical records of long-term conditions in primary care. All registered patients with a first Read v2 or SNOMED CT code for HF during the study period will be included in the study population. The clinical code lists will be made available in the GitHub repository: https://github.com/alxv/Renal-HF.

There will be no restrictions to location in terms of the population sampled. A patient’s follow-up will commence on their index (onset of HF) date and terminate on either the last date of data collection (at the practice-level), the date that they transferred out of the practice, their date of death, or the end of the study, whichever happens first. Patients will be excluded from the study if they have had a history of renal replacement therapy (dialysis, filtration, or transplant) prior to their HF diagnosis. Patients who die or are lost to follow-up before the first valid serum creatinine (t_0_) is measured are excluded from longitudinal analysis as it is not possible to determine baseline renal function. A flow diagram of criteria for inclusion/exclusion is presented in *Figure 2*.

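### Comorbidities are held at their baseline value while WRF risk is re-predicted throughout follow-up, so diagnoses coded in between are ignored

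*Protocol article*

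**What the plan says.** The Predictors section of the protocol article sets a rule with two parts: "The models will use two categories of predictors". The static part is defined as "Static predictors are baseline demographics (age, sex, ethnicity, deprivation index) and comorbidities observed at the index date". There is one exception to the timing: "If there is a gap between the index date and the first creatinine measurement, the static baseline covariates are shifted to" t0, the date of that first creatinine. The values are still taken only once.

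The dynamic part reads "Dynamic predictors will be time-varying variables updated at each measurement point, including serum creatinine, other longitudinal laboratory tests (potassium, sodium, urea"), followed by the status of active medicines. It names no diagnosis.

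The Introduction gives the purpose, which is to "predict the risk of worsening renal function (WRF) over a rolling 12-month horizon". Under Participants, patients enter on a "first ever recorded diagnosis of HF between 1 January 2005 to 1 March 2022". They are followed until last data collection, transfer out, death or the end of the study.

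**The concern.** A rolling prediction is made again and again as a patient's history grows. Under the static rule, a patient who enters in 2006 and is scored in 2016 is scored on the comorbidities recorded at baseline. A diabetes code entered in 2010 plays no part, although it is in the record at the time of prediction.

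This sits awkwardly with the project's own rationale. The Introduction criticises existing models for relying mainly on fixed risk factors and presents dynamic modelling as the advance. The likely cost is weaker separation of patients who will and will not have WRF at later prediction times, where the baseline flags are oldest. The exclusion follows from a stated rule, so it is not a detail that the article merely leaves to another document.

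**Working it through.** **Which diagnoses are covered.** The Comorbidities row of Table 1 lists chronic liver disease, diabetes, lupus and peripheral vascular disease. These fall plainly under the static rule. CKD status and history of AKI are in the Renal row; atrial fibrillation and ischaemic heart disease are in the Cardiovascular row. With only two categories, and no diagnosis named as dynamic, these most naturally fall on the static side too. That is an inference, because the dynamic list is introduced as non-exhaustive and full definitions are in Supplementary File S2, which is not shown.

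**Whether the information is available.** The Data source section says that diagnoses are coded in CPRD. They must carry dates: cohort entry depends on a first HF code within a date window, and prior renal replacement therapy is judged relative to the HF diagnosis. The data are already in longitudinal panel form with time-varying laboratory and medication values.

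**How long baseline values can be carried.** From 1 January 2005 to 1 March 2022 is 6,268 days, and 6,268 / 365.25 = 17.16 years. This is a maximum. It assumes that the study ends when the diagnosis window closes, since no separate end date is given. No median follow-up is stated.

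**How often a baseline flag would be out of date.** The plan gives no figure to reproduce and no incidence of new comorbidity. Assume a constant yearly incidence r among patients free of the condition at baseline, unrelated to leaving follow-up. The share whose flag is wrong after y years is 1 − (1 − r)^y.

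| Assumed r per year | 5 years | 10 years |
|---|---|---|
| 1% | 1 − 0.99^5 = 4.9% | 1 − 0.99^10 = 9.6% |
| 3% | 1 − 0.97^5 = 14.1% | 1 − 0.97^10 = 26.3% |
| 5% | 1 − 0.95^5 = 22.6% | 1 − 0.95^10 = 40.1% |

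The shares apply to patients who were unaffected at baseline and are still followed at that time. They measure how stale the predictor is. They do not measure a loss in C-statistic, RMSPE or calibration, which cannot be derived from the document.

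**The case against.** The strongest reply is that baseline covariates combined with a time-updated biomarker are a standard design for joint and landmark models, so this is a choice and not an error. Several parts of that reply stand.

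- **No contradiction.** A reader might infer that the static rule contradicts "All models utilize data available up to the moment of prediction". It does not. That sentence sets an upper limit on the data used, and the sentence after it, which bars future data, shows that its purpose is to prevent leakage. Baseline values respect the limit.
- **Partial recovery.** Creatinine, urea and medication are updated. They carry part of what a new CKD or AKI code would add. They stand in less directly for new diabetes or vascular disease.
- **Calibration.** A reader might infer that calibration must suffer. A model fitted and validated on baseline-defined predictors can be well calibrated for those predictors.
- **Mismatch in use.** A reader might also infer that the deployed tool would see current diagnoses and so differ from the developed model. The article does not say this, and a tool could apply the same baseline definition to dated records.
- **Age, smoking and deprivation.** Baseline age plus elapsed time largely gives current age. Smoking is named in neither category. Nothing shows that deprivation is available as a dated series.

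The reply does not explain why diagnoses already held, and known at the time of prediction, should be left out of a model meant to be dynamic. Using them adds no future information.

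**Conclusion.** The point holds as an avoidable loss of information. The plan fixes comorbidities at HF diagnosis, or at t0 if later, while predicting repeatedly over follow-up of up to about 17 years. This is certain for diabetes, peripheral vascular disease and chronic liver disease. It is probable for the renal and cardiovascular diagnoses, subject to Supplementary File S2.

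Lower discrimination at later prediction times is the likely consequence, but its size is unknown. The illustration of 5–23% out-of-date flags at 5 years and 10–40% at 10 years rests entirely on the assumed incidence of 1–5% per year. Many patients may not be followed that long. Neither an internal contradiction nor a demonstrated calibration failure is established. The change is worth making because it is cheap and serves the stated aim.

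**What to change.** In the Predictors section, move diagnoses to the dynamic set. Define each as ever coded up to t at every measurement point, and hold the value at t over the 12-month prediction window, in the same way as medication status. Sex, ethnicity, deprivation and baseline age can stay static, provided that elapsed time is in the model.

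In the secondary-outcome models, leave out the updated flag for the event being predicted (AKI hospitalization or MACE), because those models already condition on being free of it.

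If baseline-only diagnoses are intended, say so and give the reason. If Supplementary File S2 already treats some diagnoses as time-updated, bring the main text into line with it.

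The cost is some extra data preparation, refitting and checking. Replacing a baseline flag with an updated one need not add parameters. Any further terms must stay within the roughly 100 candidate parameters assumed under Sample size.

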### Sample size

The sample size calculation for the statistical models was done in accordance with Riley *et al*. to ensure adequate performance and avoid overfitting based on the expected number of predictors and prevalence of outcomes.^27^ The calculation was based on an expected prevalence of outcome of ∼25%, approximately 100 candidate predictor parameters (including non-linearity) and a target reduction factor of 0.9. For the RNN-LSTM ML approach, at least 36 000 patients are required based on the number of network parameters, published precedents in similar studies, and practical feasibility. The sample size for ML models is still under active research.^28^

### Missing data

As the longitudinal data will be anchored on the available serum creatinine measurements for each patient, we will not have any missing outcome data. Missing data for the candidate predictors will be addressed using a non-parametric imputation approach using the last measured value for a given patient as a covariate (when available) alongside other concurrent measurements.^29^ The imputation will be undertaken using the R package missForest which utilizes an iterative random forest process.

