### Data source

Using a retrospective cohort study design, we will use EHRs of HF patients to develop and validate predictive models of future renal function based on clinical and patient factors. The CPRD holds pseudonymized patient data from GP practices across the UK. In this study, we will be using records from the CPRD Aurum database for prediction model development.^19^ All predictor variables shall be derived from data collected routinely in the primary care setting. Outcome variables for hospitalization and mortality will be determined through the linkage to secondary care using hospital episode statistics and mortality data from the Office for National Statistics. In addition, the data will consist of socioeconomic status at the patient and practice-level (as a covariate and potentially for stratification) using the Index of Multiple Deprivation (IMD). In the CPRD databases, clinical diagnoses, medication, and laboratory test results are coded using a combination of Read v2, SNOMED CT, and local EMIS codes.

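### The claim that no outcome data will be missing holds for the creatinine value in each row, but not for worsening renal function within 12 months, on which the C-statistic, calibration and decision curves depend

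*Protocol article*

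**What the plan says.** The Missing data section reasons that, since each row is tied to an existing creatinine test, "we will not have any missing outcome data". It then plans imputation for candidate predictors only.

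The Outcomes section sets the endpoint: "The primary endpoint of the study will be worsening of renal function". It adds that "WRF is defined by primary care data if any of the following occur within 12 months", the qualifying events being a 30% or a 26.5 µmol/L rise in serum creatinine.

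On how creatinine is observed, the Data source section says: "Using a retrospective cohort study design, we will use EHRs of HF patients". The Introduction says: "There are no clear clinical guidelines on how renal function monitoring should be carried out in patients with HF". Under Participants, follow-up stops at the practice's last data collection or at "the date that they transferred out of the practice, their date of death, or the end of the study, whichever happens first". The only exclusion for lack of creatinine concerns the first value: "Patients who die or are lost to follow-up before the first valid serum creatinine (t_0_) is measured are excluded from longitudinal analysis".

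Under Statistical modelling, the survival part of a joint model is to deal with informative censoring by competing risks, with death and MACE as the examples. Its longitudinal part is the mixed-effects model or the growth mixture model. Under Model assessment, predictive accuracy is scored on creatinine (RMSPE), while the C-statistic, calibration and decision curves concern WRF.

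**The concern.** Anchoring a row on an existing test guarantees a creatinine at the prediction point and nothing after it. The endpoint is about what happens next. To record WRF, a later primary-care test must fall inside the window. To rule WRF out, the patient must also be followed through the window. Neither is assured in routine records with no testing schedule and with exits by transfer or end of data.

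Clinicians are likely to test patients they worry about more often, so an absent re-test probably carries information about risk. Because the article says the problem does not arise, its missing-data handling stops at the predictors.

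What is at stake is mainly evaluation. The C-statistic, calibration and net benefit all need an observed WRF status, and they inform the comparison of the three models. Leaving out one region at a time would not reveal the problem, because labels in the held-out region come from the same testing process.

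**Working it through.** **Plan's own figure.** There is none to reproduce. The article gives no re-test rate and no observed WRF rate. The expected outcome prevalence of about 25% (Sample size) is an input, taken here as the 12-month WRF rate. All other inputs below are assumptions.

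**1. When is WRF status known at a prediction point?**
- A qualifying rise at a later test in the window: WRF is known, even if follow-up then ends.
- A re-test in the window, no rise, and follow-up to 12 months: no WRF, as far as the tests show.
- No later test in the window: undetermined.
- Transfer out or end of data before 12 months with no prior event: undetermined.
- Death before 12 months with no prior event: a competing event, addressed for the two statistical models only.

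The third and fourth cases are outcome data that are missing.

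**2. No re-test, independent of WRF.** Let m be the share of points with no re-test. If these count as non-events, the recorded rate is 0.25 × (1 − m). If every unobserved point were an event, the rate would be 0.25 × (1 − m) + m.

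| m (assumed) | Recorded rate | Upper bound |
|---|---|---|
| 10% | 22.5% | 32.5% |
| 20% | 20.0% | 40.0% |
| 30% | 17.5% | 47.5% |
| 40% | 15.0% | 55.0% |

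**3. Re-testing related to WRF, unobserved points dropped.** With 90% re-tested among those with WRF and 70% among those without: 0.25 × 0.9 / (0.25 × 0.9 + 0.75 × 0.7) = 0.225 / 0.750 = 30.0%. With 90% and 50%: 0.225 / (0.225 + 0.375) = 37.5%. Dropping points therefore biases the rate upwards, while counting them as non-events biases it downwards (22.5% in both examples).

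**4. Early end of follow-up alone.** With a share c censored before 12 months, and event and censoring times uniform, the recorded rate is 0.25 × (1 − c) + 0.25 × c × 0.5. For c = 10% this is 23.8%; for c = 20% it is 22.5%. This is smaller than the effect of absent re-testing.

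**5. Testing frequency, a related issue.** One fixed creatinine process was simulated and only the number of tests was changed. Assumptions: 200,000 patients, true creatinine 110 µmol/L, annual log-slope mean 0.05 and SD 0.10, a Poisson number of tests at random times. For means of 1, 4 and 12 tests a year:
- within-person variation 10%: observed WRF 7.7%, 22.8%, 41.2%; among those re-tested at least once, 12.2%, 23.2%, 41.2%;
- within-person variation 5%: observed WRF 1.9%, 5.9%, 11.6%.

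A second simulation used other assumptions, with every patient tested at least once (median creatinine 100 µmol/L, slope SD 0.12, autocorrelated monthly values, 4% assay error). It gave about 17%, 24% and 32%. The direction is the same throughout and the size is not. The gradient persists among re-tested patients, so it is not only a missing-outcome effect: any qualifying rise counts, and more noisy tests give more chances to cross the threshold.

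**The case against.** The strongest defence is that the outcome in that sentence means the modelled response. The Prediction models and Statistical modelling sections fit continuous creatinine, which every row has by construction, and RMSPE is scored on observed values. Read that way, the sentence is correct. Likelihood-based mixed models also tolerate irregular testing that depends on recorded history. This stands, and it limits the point to WRF.

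It also rules out a stronger reading that a reader might infer: that rarely tested patients would be trained to look safe, and that the tool would then recommend fewer tests for them. No binary WRF label is fitted. WRF probability is derived from forecast trajectories, and the recommendation module works from forecast creatinine with a NICE guideline as its backbone. An effect on training or recommendations is possible, but the article does not show one.

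A reader might also infer that undetermined points are silently dropped or counted as no WRF. The article states no such rule; it states none at all for these points.

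The joint model is a real provision, and death as a competing event is already in the plan. It does not mention absent re-testing or transfer out, and no counterpart is described for the RNN-LSTM.

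Finally, Supplementary Files S3 and S4 are not shown and may define which points are evaluable. The absence of a scheme is therefore not the criticism. The criticism is of the sentence, which no supplement can make true of 12-month WRF.

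**Conclusion.** The point holds for the primary endpoint. The article rules out missing outcome data for a reason that covers only the creatinine value in each row, while WRF within 12 months can be undetermined through absent re-testing, transfer out or end of data. The main consequence is for the WRF performance measures and for the model comparison that uses them.

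The direction is clear once a way of treating undetermined points is chosen. The size cannot be read from the article. With an assumed 10–40% of points lacking a re-test, independent of WRF and counted as non-events, 25% is recorded as 22.5–15%. If re-testing is related to WRF and undetermined points are dropped, the examples give 30.0–37.5%. Dependence on testing frequency comes on top, and its size varies widely with the assumed creatinine variation.

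**What to change.** - Limit the Missing data sentence to the creatinine response.
- For WRF evaluation, class each prediction point as WRF, no WRF (with a qualifying re-test in the window, defined in advance) or unobserved.
- Use only prediction points with a potential 12-month window before the data end.
- In the WRF performance measures of all three models, weight by the inverse probability of being re-tested and of remaining uncensored, given history up to the prediction time. Treat death as a competing event, consistently with the joint model.
- Report two sensitivity analyses: complete case, and unobserved counted as no WRF.
- Report performance by testing frequency. Weighting for any re-test does not remove the frequency effect; where every patient has at least one test, re-test weighting leaves the gradient unchanged.

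The cost is analytical only, on data already extracted: an added model of testing and censoring within each validation fold, and somewhat wider intervals. Inverse-probability weighting is one workable choice among several. The classification into three states is needed whichever is used.
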